### Data collection

Data for the effect evaluation were gathered by means of self-administered questionnaires, fall calendars, and telephone interviews. Trained interviewers, who were blinded for group allocation, conducted the interviews. After baseline measurement participants received a fall calendar; every three months a sheet of the calendar was to be returned to the research team. Data for the process evaluation collected from the participants were completed by means of self-administered questionnaires and short telephone interviews. Registration forms and self-administered questionnaires were used to gather data from the facilitators. These data were discussed and illustrated by the facilitators in two evaluative meetings.

As recommended by Hollis and Campbell [38], non-compliant participants of the intervention group were approached for all follow-up measurements and participants with missing data were contacted to ensure completion of data. At five and 11 months after the intervention, newsletters were sent to keep the participants interested in participating in the trial and to notify them about its progress.

### Sample size and power

Sample size calculations were based on experiences in evaluative studies among older persons in the Netherlands [39] and the US [15] where fall-related self-efficacy [7] was assessed. To detect a mean difference of at least 2.5 points on fall-related self-efficacy between the intervention and control group (SD is 6.0; equivalent to an effect size of .42), at least 117 participants in each group were necessary to meet a power of 80 percent at alpha .01 (one-sided). Taking a dropout rate of 30 percent during the trial into account, a total number of 180 participants per group (n = 360) were needed to enrol in the trial. Based on unpublished data of [name] and colleagues (study described in [39]), we estimated that approximately 14.5 percent of the older persons who returned the screening questionnaire would meet all inclusion criteria and exclusion criteria and would be interested in participating in the trial. With an estimated response rate of 55 percent, a minimum sample of 4500 older persons aged 70 or over needed to be approached with a screening questionnaire.

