### Randomisation

Randomisation was carried out directly after baseline measurement and was performed per community to ensure having both an intervention group and a control group in each of the two communities. During each cycle two intervention groups were composed per community. Per cycle, approximately half of the participants were allocated to the intervention group (with a maximum of 15 participants per intervention group). Participants allocated to the intervention group were then randomly allocated to one of the two groups in their own community. Participants allocated to the control group received no intervention as a result of this trial. An independent researcher conducted randomisation by selecting random samples using SPSS12.0 for Windows.

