### Intervention

The intervention AMB-NL is a translated and adapted version ([name], et al., development of intervention protocol, submitted) of a cognitive behavioural group intervention for older persons living in the community developed by Tennstedt and colleagues [15]. This intervention has been developed to reduce fear of falling and promote physical, social, and functional activity in elderly persons living in the community. Principles of cognitive restructuring [17] are applied by focusing on changing attitudes and self-efficacy beliefs with respect to falling before attempting to change actual behaviour. To attain a reduction in fear of falling, the intervention aims to increase self-efficacy beliefs with regard to falling as well as the sense of control over falling. Four strategies are used to accomplish these aims: (1) restructuring misconceptions to promote a view of fall risk and fear of falling as controllable; (2) setting realistic goals for increasing activity; (3) changing the environment to reduce fall risk; and (4) promoting physical exercise to increase strength and balance [15].

The intervention consists of eight weekly group sessions lasting two hours. Six months after the eighth session a booster session is scheduled. The main topics in each of the sessions of AMB-NL, presented in table 1, were discussed similarly: (1) introduction; (2) participant's point of view; (3) positive and negative aspects concerning the topic; (4) association with falls or fear of falling; and (5) implementation in the participant's daily life. A more extensive description of the intervention will be published elsewhere ([name] et al., development of intervention protocol, submitted).

**Table 1 T1:** Main contents of the Dutch version of AMB (AMB-NL)

Session contents of AMB-NL

Session 1: Introduction to the Program

Starting a group intervention (e.g. getting acquainted)
Background information on fear of falling (e.g. incidence, impact)
Beliefs and disbeliefs about fear of falling
Shifting from negative to positive thinking patterns
Finding personal solutions to deal with fear of falling

Session 2: Exploring Thoughts and Concerns about Falling

Attitudes related to fear of falling and challenging them
Adaptive responses to counter misconceptions about falls
Unhelpful thoughts and their effects regarding to feelings and behaviour
Shifting from self-defeating to self-motivating thoughts

Session 3: Exercise and Fall Prevention

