### Analysis

Descriptive techniques will be used to describe participants of the trial. To detect differences between intervention and control group, baseline variables will be compared using the appropriate tests. Baseline variables of compliant and non-compliant participants of the intervention group will be compared as well. Compliant participants are participants who attended five or more sessions [15], not including the booster session.

Data of the effect evaluation will be analysed according the intention-to-treat and on-treatment principle. Univariate and multivariate techniques will be applied to examine the differences in the intervention and control group with regard to the primary and secondary outcome measures at the follow-up measurements. Effect sizes [40] will be calculated to quantify the size of the difference between both groups. Subgroup analysis will be performed with several potential effect modifiers, like cognitive status or educational level.

Data of the process evaluation will be analysed using descriptive techniques.

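### The figure of 117 per arm assumes independent participants, although the intervention is delivered in 20 therapy groups; restate the power and name a therapy-group term in the effect analysis

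*Protocol article*

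**What the plan says.** In the protocol article, Sample size and power builds its target from four inputs: a difference, an SD, an alpha and a power.

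- The difference and SD: "To detect a mean difference of at least 2.5 points on fall-related self-efficacy between the intervention and control group", with "SD is 6.0; equivalent to an effect size of .42".
- The result: "at least 117 participants in each group were necessary to meet a power of 80 percent at alpha .01 (one-sided").
- The enrolment target, which the section explains only by an expected 30% loss to dropout: "a total number of 180 participants per group (n = 360) were needed to enrol in the trial".

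The section mentions no ICC, design effect or therapy group.

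Other sections describe grouped delivery in one arm only. Intervention says: "The intervention consists of eight weekly group sessions lasting two hours". Randomisation forms two intervention groups per community in each cycle, with at most 15 people in each, and says: "Participants allocated to the intervention group were then randomly allocated to one of the two groups in their own community". Study design gives five cycles, and Settings and locations gives two communities. After the first session, one facilitator leads each session. Controls receive no intervention from the trial.

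Analysis says only: "Univariate and multivariate techniques will be applied to examine the differences in the intervention and control group". Progress of the study reports 260 people allocated to intervention and 280 to control.

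**The concern.** People treated in the same group share a facilitator, peers and discussion over eight sessions. Their outcomes may therefore be positively correlated, while the controls' outcomes are not correlated in this way. This is a partially nested design, and the mean of the intervention arm is less precise than the head count suggests.

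Two things are at stake. First, a sample size set at exactly 80% power under independence falls short of 80% once the correlation is appreciable. Second, an analysis that treated all participants as independent would use too small a standard error. It would then reject too often and give intervals that are too narrow. The article ties a recommendation to implement the intervention in Dutch health care to a positive result, so control of false positives matters.

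**Working it through.** **Inputs from the article.** Difference 2.5; SD 6.0; one-sided alpha 0.01; power 80%; 117 per arm; 180 per arm enrolled; dropout 30%; 260 and 280 allocated.

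**Derived.** Number of therapy groups = 5 cycles x 2 communities x 2 groups = 20. As a check, 260/20 = 13 per group, within the limit of 15.

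**Assumed.** The article gives no ICC, so 0.02, 0.05 and 0.10 are used as an illustrative range. Groups are taken as equal in size and 6.0 as the total SD.

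**Step 1: reproduce the stated figure.** Normal approximation for independent observations: n = 2 x ((2.326 + 0.842) x 6.0/2.5)² = 115.6, so 116 per arm. The exact t-test calculation gives 117, with power 80.01%. The stated figure is therefore the independent-observations result, with a design effect of 1.

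**Step 2: allow for clustering in the intervention arm only.**

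- Mean evaluable group size: m = n_int/20
- Design effect: DE = 1 + (m − 1) x ICC
- Standard error: SE = 6.0 x √(DE/n_int + 1/n_ctrl)
- Power = Φ(2.5/SE − 2.326)

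Worked example at 117 per arm and ICC 0.05: m = 5.85; DE = 1 + 4.85 x 0.05 = 1.242; SE = 6.0 x √(2.242/117) = 0.831; power = Φ(3.01 − 2.33) = 75.3%.

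**Step 3: true error if the groups were ignored.** A test at nominal one-sided 1% that used the independence standard error SE₀ = 6.0 x √(1/n_int + 1/n_ctrl) would have true error 1 − Φ(2.326 x SE₀/SE). Example at 182 and 196 with ICC 0.05: SE₀/SE = 0.909, so the error is 1 − Φ(2.115) = 1.72%.

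**Results** (in the last three columns, values are for ICC 0.02 / 0.05 / 0.10):

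| Evaluable (intervention / control) | m | Power at ICC 0 | DE | Power, % | True error if groups ignored, % |
|---|---|---|---|---|---|
| 117 / 117 (stated minimum) | 5.85 | 80.5 | 1.097 / 1.242 / 1.485 | 78.4 / 75.3 / 70.3 | 1.15 / 1.40 / 1.84 |
| 126 / 126 (180 less 30%) | 6.30 | 83.7 | 1.106 / 1.265 / 1.530 | 81.5 / 78.3 / 73.0 | 1.17 / 1.44 / 1.93 |
| 182 / 196 (260 and 280 less 30%) | 9.10 | 95.7 | 1.162 / 1.405 / 1.810 | 94.1 / 91.2 / 85.8 | 1.27 / 1.72 / 2.55 |

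The powers use the normal approximation, which at 117 and ICC 0 gives 80.5% against the exact 80.01%.

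**Step 4: where 80% is lost.** With 126 evaluable per arm, power stays at or above 80% up to an ICC of about 0.034. With 182 and 196, it does so up to about 0.15. Holding 20 groups fixed, 80% power needs 122, 132 or 155 evaluable per arm at ICC 0.02, 0.05 or 0.10. At 30% dropout that is 175, 189 or 222 enrolled per arm.

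The larger recruited sample restores power but does not reduce the error inflation. More people in the same 20 groups means larger groups and a larger design effect.

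**Limits.** The calculation has no small-sample correction for 20 groups, no facilitator-level clustering, and no dilution from people who never attended.

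**The case against.** The strongest objection concerns the analysis. A reader might infer that the plan commits to an analysis that treats participants as independent. The article does not support that. Its Analysis section names no model, covariates or random effects, and neither includes nor excludes a therapy-group term. A condensed article may leave such detail to an analysis plan that is not shown. The error figures are therefore conditional on a choice the article has not made. This part of the objection stands.

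A reader might also infer that the trial is underpowered. That is not supported either. The 180 planned per arm exceeds 117/0.7 = 167.1, so 168, and the slack keeps 80% power at low ICCs, although the article explains the 180 by dropout alone. With the 260 and 280 allocated, power stays above 80% across the whole assumed range.

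Third, the size of the problem depends on an ICC that the article does not give. Random assignment to groups within a community rules out self-selection as a source of correlation. Absentees were contacted individually, and an intention-to-treat arm includes people with little group exposure, which could dilute the correlation. This is fair, and at an ICC of 0.02 the loss at 117 is about 2 points. But randomising people into groups does not prevent correlation that arises afterwards from a shared facilitator and peers.

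None of this changes the sample-size point: the stated calculation uses a design effect of 1 for a design that is grouped in one arm.

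**Conclusion.** The point holds for the sample-size statement. The 117 per arm and its 80% power rest on full independence, which does not fit delivery in 20 therapy groups. Over assumed ICCs of 0.02 to 0.10, power at that number is about 78 to 70% rather than 80%, and at the planned 126 evaluable about 81.5 to 73%.

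It does not extend to a power shortfall in the trial as recruited, where power is about 94 to 86% at 30% dropout. No extra enrolment is needed.

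For the analysis it is a conditional caution. If therapy group were left out, a nominal one-sided 1% test would have a true error of about 1.3 to 2.6% with the recruited numbers. One-sided 1% is the only level the article states, so no inflation is claimed at any other level.

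**What to change.** 1. Restate the power for the number actually randomised, with a design effect in the intervention arm only, over a stated range of ICCs.
2. Before the effect data are analysed, specify a partially nested mixed model for the effect outcomes. It should have a random effect for the 20 therapy groups in the intervention arm, each control treated as a singleton, and small-sample degrees of freedom (Satterthwaite or Kenward-Roger). Keep each participant in the therapy group as assigned, whatever their attendance.
3. Report the estimated ICC with the results.

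The cost is a few lines of analysis text and one model term. Groups were assigned by randomisation and facilitators recorded attendance, so membership should be recoverable. Intervals become slightly wider and the stated power slightly lower. The article reports preparations only for analysing the screening and process data, so the effect model can apparently still be fixed in advance.

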### Analysis

Descriptive techniques will be used to describe participants of the trial. To detect differences between intervention and control group, baseline variables will be compared using the appropriate tests. Baseline variables of compliant and non-compliant participants of the intervention group will be compared as well. Compliant participants are participants who attended five or more sessions [15], not including the booster session.

Data of the effect evaluation will be analysed according the intention-to-treat and on-treatment principle. Univariate and multivariate techniques will be applied to examine the differences in the intervention and control group with regard to the primary and secondary outcome measures at the follow-up measurements. Effect sizes [40] will be calculated to quantify the size of the difference between both groups. Subgroup analysis will be performed with several potential effect modifiers, like cognitive status or educational level.

Data of the process evaluation will be analysed using descriptive techniques.

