## Background

Fear of falling and associated activity restriction are common in elderly persons, both in those older persons who have experienced a fall and those who have not [1,2]. Studies in older people living in the community showed that about 20 to 60 percent of these persons experience at least some fear of falling [2-6] and about 20 to 55 percent report activity restriction due to fear of falling [1,5,7-9]. In this paper, we focus on the design of a randomised controlled trial evaluating a cognitive behavioural group intervention, which aims to reduce fear of falling and associated activity restriction in elderly persons.

In one of the first reported studies on fear of falling, Vellas and colleagues indicated that fear of falling may lead to a debilitating spiral marked by loss of confidence and reduced activity, resulting ultimately in a loss of independence [10]. In later studies this observation was strengthened. Fear of falling was found to be associated with several adverse factors, including decreased quality of life [3,11], decreased mobility [3,11], functional decline [3,11,12], falls [13], and institutionalisation [11]. These factors may not only have an adverse influence on the physical health status of elderly persons, but on the social and mental health status as well. Therefore, reducing fear of falling and associated activity restriction in older persons may improve their health status. However, until now only a few interventions have been developed and evaluated specifically to reduce fear of falling in elderly people living in the community [14-16].

In our trial we will evaluate one of these interventions in the Netherlands, a cognitive behavioural group intervention called A Matter of Balance (AMB). This intervention has originally been developed and evaluated in the US and aims to reduce fear of falling and associated activity restriction in elderly persons [15]. The intention-to-treat analysis showed statistically significant effects for increased activity (mobility and intended activity) directly after the intervention. The on-treatment analysis (including participants who attended five or more out of eight sessions) showed statistically significant improvement in falls efficacy, perceived ability to manage falls, and activity (mobility) directly after the intervention. At 12 months, this latter group showed statistically significant improvement in falls efficacy and activity (mobility range and social function).

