Nurses qualified in the field of geriatrics and working for home care agencies were trained as facilitators of the intervention. Except for the first session when two facilitators were present, each intervention session was conducted by one facilitator. Monthly meetings with facilitators and researchers were scheduled to evaluate and discuss the progress of the trial, the intervention and associated matters. Participants were informed to notify the facilitators or researchers if they were unable to attend a session. After the session, facilitators contacted those participants who were absent and briefly discussed the topics of that session. However, those participants who were absent in all of the first three sessions were excluded from further participation in the intervention due to an unbridgeable deficiency in knowledge.

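### Intention-to-treat and on-treatment analyses are given equal standing, although the on-treatment contrast is not protected by randomisation and can show benefit where there is none

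*Protocol article*

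**What the plan says.** The Analysis section of the protocol article reads: "Data of the effect evaluation will be analysed according the intention-to-treat and on-treatment principle". The Methods/design part of the Abstract says the same. Neither analysis is called primary, supportive or sensitivity, and the sentence covers all primary and secondary outcomes.

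The preceding paragraph of the Analysis section defines compliance: "Compliant participants are participants who attended five or more sessions [15], not including the booster session". It cites the earlier US trial for the cut-off. The Background describes that trial's on-treatment set by the same rule: "The on-treatment analysis (including participants who attended five or more out of eight sessions) showed statistically significant improvement in falls efficacy". Its intention-to-treat result is given as: "The intention-to-treat analysis showed statistically significant effects for increased activity (mobility and intended activity) directly after the intervention".

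On the control arm, the Randomisation section says: "Participants allocated to the control group received no intervention as a result of this trial". On absentees, the Intervention section says that "facilitators contacted those participants who were absent and briefly discussed the topics of that session", and that "those participants who were absent in all of the first three sessions were excluded from further participation in the intervention".

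The Data collection section adds that non-compliant intervention participants were approached for every follow-up measurement. The Analysis section also plans a baseline comparison of compliant and non-compliant participants, and univariate and multivariate techniques.

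**The concern.** Attendance is settled after randomisation. It plausibly depends on health, mobility, cognition and motivation, which also bear on fear of falling, avoidance and daily activity. The article itself offers transport to people who expect trouble reaching sessions, for instance because of health problems (Settings and locations). An untreated control arm contains people who would not have attended, but they cannot be identified and removed. Dropping low attenders from one arm only leaves two groups that randomisation no longer makes comparable.

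This matters because the two analyses can disagree and nothing says which one prevails. The Background lists falls efficacy among the US trial's significant results only for the on-treatment analysis, and fall-related self-efficacy is the outcome on which the present trial was sized. The Future implementation section makes roll-out depend on the results showing effectiveness, without saying which results. If a similar pattern appeared here, a claim of effectiveness could rest on selection.

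**Working it through.** **Inputs from the article.** Design difference 2.5 points, SD 6.0, one-sided alpha 0.01, power 80 percent, 117 per group, 30 percent dropout (Sample size and power); 260 allocated to intervention and 280 to control (Progress of the study).

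**The plan's own figure.** n per group = 2 × (z0.99 + z0.80)² × SD² / difference² = 2 × (2.326 + 0.842)² × 36 / 6.25 = 115.6, so 116. The t-test version gives 116.98, so 117. The stated 117 reproduces with a one-sided test at 0.01; the two-sided version gives 135 and does not fit. SD 6.0 and one-sided 0.01 are therefore used below.

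**Assumed inputs, not in the article.** c, the share of the intervention arm attending five or more sessions: 0.5 to 0.8. d, the amount by which attenders would score better than non-attenders without any treatment: 1 to 3 points (0.17 to 0.50 SD).

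**Bias under no treatment effect.** By randomisation, the control mean is the mixture c × (attender mean) + (1 − c) × (non-attender mean). Subtracting this from the attender mean gives

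bias = (1 − c) × d.

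**Rejection rate.** SE = 6 × √(1/(260c) + 1/280), and the rate is 1 − Φ(2.326 − bias/SE). With 30 percent dropout in both arms, unrelated to attendance, SE is divided by √0.7.

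**Worked case, c = 0.7, d = 3.** Bias = 0.3 × 3 = 0.9 points. Attenders = 260 × 0.7 = 182. SE = 6 × √(1/182 + 1/280) = 0.571. Rate = 1 − Φ(2.326 − 1.575) = 0.226. With dropout, SE = 0.683 and the rate is 0.157.

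| c | d (points) | Bias (points) | Rate, no dropout | Rate, 30% dropout |
|---|---|---|---|---|
| 0.8 | 1 | 0.2 | 0.025 | 0.022 |
| 0.8 | 2 | 0.4 | 0.055 | 0.043 |
| 0.8 | 3 | 0.6 | 0.109 | 0.079 |
| 0.7 | 1 | 0.3 | 0.036 | 0.030 |
| 0.7 | 2 | 0.6 | 0.101 | 0.074 |
| 0.7 | 3 | 0.9 | 0.226 | 0.157 |
| 0.6 | 1 | 0.4 | 0.049 | 0.039 |
| 0.6 | 2 | 0.8 | 0.161 | 0.113 |
| 0.6 | 3 | 1.2 | 0.373 | 0.257 |
| 0.5 | 1 | 0.5 | 0.062 | 0.048 |
| 0.5 | 2 | 1.0 | 0.225 | 0.156 |
| 0.5 | 3 | 1.5 | 0.512 | 0.361 |

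With d = 0 the rate stays at 0.010 for every c. With d negative the bias runs against the intervention. The intention-to-treat comparison of 260 with 280 has no selection bias of this kind, and its rate is 0.010.

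**The case against.** **The comparator is not written out.** The five-session rule is given for a baseline comparison of compliers and non-compliers, and the on-treatment set is never defined. This stands: attenders of five or more sessions against all controls is an inference. It is a close one, because the cut-off is taken from the US trial, that trial's on-treatment set used it, and untreated controls cannot be selected on attendance.

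**Ranking may sit in a fuller document.** A journal article condenses, and an analysis plan may name the primary population. A reader might infer that this plan lets the on-treatment result decide effectiveness; the article does not say so. But the point is not only an omission. The article commits the effect evaluation to both analyses side by side, and one of them breaks randomisation.

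**Safeguards exist.** Non-compliers were followed up, compliers and non-compliers are to be compared at baseline, multivariate methods are planned and baseline outcome values are collected. This also stands. Adjustment could shrink the bias, and the figures above are for an unadjusted contrast. The baseline comparison shows measured imbalance without correcting it, and no adjustment is tied to the on-treatment analysis.

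**The US trial.** A reader might infer that its intention-to-treat result for falls efficacy was null. The Background does not say that: it lists significant findings only and reports no 12-month intention-to-treat result. Non-mention suggests a divergence but does not establish it.

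**The inputs are assumed.** Attendance share, prognostic gap and direction are not in the article, and dropout unrelated to attendance is a simplification. A reader might infer that the bias must favour the intervention; if attenders were the more fearful group, it would not.

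**The alternative estimator has its own weakness.** Calls to absentees mean that allocation may act on people who attended nothing, which strains the exclusion restriction of an instrumental-variable estimate. This is right and has to be stated in the plan.

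**Conclusion.** The point holds in a limited form. The article gives equal standing to intention-to-treat and to an on-treatment analysis which, by close inference, sets a self-selected part of one arm against the whole of the other. That analysis can produce an apparent benefit without a treatment effect if attenders have the better prognosis.

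Across the assumed range, the error rate of the nominal 1 percent test runs from little more than double its nominal level to about half of all trials. The top of that range needs both low attendance and a gap of half an SD. These rates illustrate the mechanism for an unadjusted contrast; they are not predictions for this trial. What is secure is that the ranking is missing and that the on-treatment contrast lacks the protection of randomisation.

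**What to change.** State in the Analysis section that intention-to-treat alone decides effectiveness and that any attendance-based analysis is supportive. The follow-up of non-compliers makes a full intention-to-treat analysis feasible. The article reports that effect data were not yet available, so this can be settled beforehand.

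In place of attenders against all controls, use a complier-average causal effect that keeps everyone as randomised, with allocation as the instrument (for example by two-stage least squares) and attendance at any session as the main definition of treatment received. Because controls cannot attend, the simple form is the intention-to-treat difference divided by the share attending. It is therefore zero when allocation has no effect.

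Write down its assumptions. Allocation must act on the outcome only through attendance; the calls to absentees may breach this. A five-session definition, if kept as a sensitivity analysis, breaches it further, because people attending one to four sessions are also treated. The estimate would then be too large if partial attendance helps.

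Cost: a few sentences in the plan, one extra model, and a wider interval than the on-treatment analysis would give.
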